**Inclusion criteria:**
a) Age between 50 and 85 years
b) Age and education corrected mini-mental state examination score equal or superior to 24/30
c) Clinical Dementia Rating (CDR) global score of 0.5
d) Concerns about cognitive modifications, expressed as subjective complaints by the subject, or by impression by a close acquaintance or an expert clinician
e) Defective performance with reference to age and education matched controls in one cognitive domain (memory, executive function, attention, language, visuospatial function): if repeated assessments are available, evidence of performance decline
f) Preserved functional autonomy: the subject remains fully independent, even if specific performances may be slower, less efficient than usual level, with occasional errors
g) No dementia: the cognitive modifications do not significantly hamper social function or work activities

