### Statistical analysis method

All the analysis will be conducted on patients with the baseline assessment of biomarkers available; consequently, patients without biomarker assessment will be excluded from the primary analysis.

To exclude selection bias, a comparison of baseline characteristics of individuals not included in the analysis due to incomplete biomarkers assessment and those included in the analysis will be performed.

A multivariable predictive model of conversion to AD will be developed including biomarkers, socio-demographic and clinical predictors. The evaluation of biomarkers for MMSE, DFR, CSF parameters and MRI measures will be conducted considering the continuous form and the categorical form applying validated cut-offs.

For the MMSE [24], a cut-off of 24 (< 24) for the age- and sex-corrected score will be used, as indicated in the literature [25]. For the correction of the crude score, Measso et al. [26] will be used for individuals aged ≤ 64, and Magni et al. [25] will be used for those aged > 64. Regarding the DFR, a test result will be classified as abnormal if the age-adjusted score is ≤ 6.31 [27].

For MRI, measurements of the right and left hippocampus are considered for each technique, ACM-Adaboost and Freesurfer, and atrophy is defined below the 5th percentile according to the age-specific thresholds defined for individuals aged 56–90 years, as published [12]. For individuals aged 50–55 years, the cut-offs are extrapolated from the 5th percentile function (see Additional file 2). Right and left hippocampal atrophy measured with the two techniques will be analysed separately.

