For CSF biomarkers, p-tau, t-tau, Aβ1-42, Aβ_1-42/1–40_ ratio and Aβ_1-42_ /p-tau ratio will be evaluated separately. The cut-offs used for each biomarker are reported in Table 3 along with the literature references [28–31]. For the EEG, the classification of results into normal or abnormal based on the SW values will be performed by the expert centre using a machine learning (ML) method based on fine Gaussian support vector machine. This ML classification model has been trained on external data including both healthy individuals and individuals with AD [32] and will be applied to the study cohort. The FDG-PET result will be categorised as either positive or negative by the evaluators at the expert centre based on the methodology previously described [10, 11]. In the case of FDG-PET positivity, it will also be specified whether it is indicative of an AD-like form or other forms of dementia. The APOE-e4 genotype will be classified as none, one (heterozygosis), or both alleles (homozygosis) (see Table 3 and Additional file 3 for details of the cut-offs and literature references).

**Table 3 Tab3:** Reference value for identifying abnormal values by biomarkers

Biomarker	Reference value for categorisation	Literature and notes
**MMSE**	Age- and sex-adjusted score < 24	Applied correction factors from Measso et al. [26] for age ≤ 64 and Magni et al. [25] for age > 64
**DFR**	Age-adjusted score ≤ 6.31	Frasson et al. 2011 [27]
**Hippocampal volume**	< 5° percentile of the normative population	De Francesco et al. 2021 [12]; see Additional file 3

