**CSF biomarkers**		
Aβ (1–42)	≤ 640 pg/ml	Bellomo et al. 2021 [28]
Total-tau	≥ 404 pg/ml	Bellomo et al. 2020 [29]
Phosphorylated Tau 181 (p-Tau)	≥ 56 pg/ml	Bellomo et al. 2020 [29]
Ratio Aβ_1-42/1–40_	≤ 0.068	Doecke et al. 2018 [30], Leitão et al. 2019 [31]
**Ratio** Aβ_1-42 /p-Tau_	≤ 11.8	Leitão et al. 2019 [31]
**EEG**	Classified in physiological vs pathological based on Small World for the seven EEG frequency bands using machine learning technique	Vecchio et al. 2023 [32]
**FDG-PET**	Classified in negative and positive (AD-like, other forms) using the optimised SPM procedure	Della Rosa et al. 2014 [10], Perani et al. 2014 [11]
**APOE- e4**	Classified in none, one allele, both the alleles	

However, these cut-offs were determined to discriminate between normal cognition and AD, but the population under study is at higher risk of developing dementia compared to the normal population. Therefore, for continuous biomarkers the receiver operating characteristic (ROC) curves will be used to identify new optimal cut-offs for the specific population under study. For biomarkers known to be influenced by sex and/or age, the corrected values will be used. In this context, sensitivity and specificity are both considered targets for determining the optimal cut-off; therefore, among all the commonly used methods [33], the distance to the left-upper corner was chosen. This method maximises both sensitivity and specificity and guarantees a better balance between the two measures [34]. Warnings are raised about its use as not always the method leads to an optimal cut-off in the intention of maximising overall correct classification rates compared to the commonly used Youden’s method [35]; therefore, Youden’s method will be also provided for comparison.

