#### Statistical model and variable selection

Initially, an analysis of socio-demographic and clinical variables will be conducted using the Cox model to identify a core of variables significantly associated with the outcome that will be included in the development of the prognostic multivariable model. A check of multicollinearity between predictors will be assessed, then a stepwise selection starting from the full model will be applied using a threshold of 0.10 for removal and 0.05 for re-admission of variables. A final check of variables not selected by stepwise will be conducted using the likelihood ratio test [36, 37]. Age and sex will be forced in the procedure selection and retained in the final model. Subsequently, these selected variables will be included in multivariable models with the addition of individual biomarkers one at a time. The additional predictive value of each biomarker beyond clinical and socio-demographic variables will be calculated. The performance results will be used to determine for each biomarker which form (continuous or categorical) will be chosen for the development of the multivariable prediction model. Categorisation is typically preferred for the application in clinical practice, but as any categorisation implies a loss of information, we will select the biomarker in a categorical form if the loss in performance could be considered negligible with respect to the continuous form. Categorisation will also be chosen in cases where non-linearity is detected for the continuous form. The categorisation according to the threshold provided by the experts (Table 3) will be preferred in case a small loss of performance is observed compared to the continuous form.

The final predictive model will be identified through a multivariable model considering as eligible predictors all the biomarkers and all selected predictors among the clinical and socio-demographic variables using the stepwise selection procedure as described above. Age and sex will be forced into the model selection process. A final check of the result from the automatic selection procedure will be conducted to ensure that no significant biomarkers were excluded and, vice versa, that no negligible biomarkers were included.

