#### Predictive performance

For each biomarker in the categorical form, the accuracy measures (sensitivity, specificity, positive predictive value, negative predictive value, overall accuracy, positive and negative likelihood ratios) will be calculated for comparison with the literature. For continuous biomarkers, the area under the receiver operating characteristic curve (AUC) will be also reported. Moreover, a univariate analysis will be conducted using the proportional hazard Cox model.

To evaluate the performance of the prediction models, several measures will be considered. The concordance c-index with its 95% CI will be provided as a discrimination measure and the extensions of binary AUC to survival analysis proposed by Harrell will be used [40, 41]. The Akaike information criterion will be provided as a measure of the goodness of fit of the model.

The added value on performance of each biomarker to the multivariable model with demographical and clinical variables will be assessed by the category-free Net Reclassification Improvement (NRI), which is the net proportion of events reclassified correctly plus the net proportion of non-events reclassified correctly. The delta AUC (difference in c-statistics) will be also provided [41], and the likelihood ratio test will be used to assess the statistical significance of the incremental contribution of each biomarker [36, 37].

In addition, to assess the predictive performance of the final multivariable model, calibration measures will also be reported [38, 42]. A calibration plot will be done by plotting the observed outcome proportion (on the *y*-axis) versus the ordered predicted outcome probabilities (on the *y*-axis) by quantile of the predicted risk. Subsequently, the calibration intercept and slope and their 95% CI will be estimated. There is a perfect calibration when the intercept is zero and the slope is one. Moreover, overall measures of performance, the Nagelkerke’s *R*^2^ and the Brier score, will be provided. The Brier score is a composite measure of discrimination and calibration with lower scores indicating improved model accuracy, and it will be calculated at a fixed time point (3 years).

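### The Table 3 cut-off for an abnormal MMSE (below 24) is the complement of the entry criterion (24 or above), so that category is empty or nearly empty by design

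*SAP article*

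**What the plan says.** **Entry.** Table 1, inclusion criterion b, requires: "Age and education corrected mini-mental state examination score equal or superior to 24/30".

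**Analysis.** The section Statistical analysis method plans that MMSE, with several other biomarkers, "will be conducted considering the continuous form and the categorical form applying validated cut-offs". For MMSE, "a cut-off of 24 (< 24) for the age- and sex-corrected score will be used". Table 3 repeats this: "Age- and sex-adjusted score < 24".

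**Use of the category.** The section Predictive performance plans a full set of measures: "For each biomarker in the categorical form, the accuracy measures (sensitivity, specificity, positive predictive value, negative predictive value, overall accuracy, positive and negative likelihood ratios"), for comparison with published values. The section Statistical model and variable selection adds a preference: "The categorisation according to the threshold provided by the experts (Table 3) will be preferred in case a small loss of performance is observed", the comparison being with the continuous form. The same section also turns to categorisation when a continuous biomarker proves non-linear.

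**Alternative cut-offs.** The paragraph after Table 3 concedes that the listed thresholds were set to separate normal cognition from AD. It adds that "for continuous biomarkers the receiver operating characteristic (ROC) curves will be used to identify new optimal cut-offs for the specific population under study".

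**The concern.** The threshold that defines an abnormal MMSE is the one that keeps people out of the study. A variable coded this way is constant, or close to it, before any data are seen. The plan nevertheless asks for its sensitivity, predictive values and likelihood ratios, and gives its threshold preference over others when little performance is lost.

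Two things are at stake. First, the accuracy row for MMSE would be set against published figures although the entry rule largely fixes it. Second, the selection rule could carry an uninformative coding of a named study biomarker into the final model building.

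The two places also describe the correction differently: age and education at entry, age and sex in the analysis. The article does not explain the difference.

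**Working it through.** **Inputs from the article.** Entry: corrected MMSE 24 or more (Table 1). Abnormal: corrected MMSE below 24 (Statistical analysis method, Table 3). From Sample size: 400 evaluable participants, AD incidence 40% (Table 2 also uses 27% and 35%), working sensitivity 80%, literature sensitivity 52 to 81%. The share q of the cohort scoring below 24 is not given, so it is an assumption, shown as a range.

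**1. The plan's own figures.** Half-width for sensitivity = 1.96 × √[p(1 − p)/(400 × incidence)]; for specificity, replace incidence by 1 − incidence. At p = 80%:

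| Incidence | Sensitivity, computed | Table 2 | Specificity, computed | Table 2 |
|---|---|---|---|---|
| 27% | 7.54% | 7.5% | 4.59% | 4.6% |
| 35% | 6.63% | 6.6% | 4.86% | 4.9% |
| 40% | 6.20% | 6.2% | 5.06% | 5.1% |

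The other twelve cells also reproduce to rounding, and 400/(1 − 0.20) = 500. Nothing in Table 2 is wrong. The question is whether MMSE below 24 can come near the sensitivities it assumes.

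**2. Same score in both places (q = 0).** At 40% incidence there are 0.40 × 400 = 160 converters and 240 non-converters, all coded normal.
- Sensitivity = 0/160 = 0%; specificity = 240/240 = 100%.
- Positive predictive value = 0/0 and positive likelihood ratio = 0/(1 − 1): both undefined.
- Negative likelihood ratio = (1 − 0)/1 = 1.
- Negative predictive value and overall accuracy = 240/400 = 60%, which is only the share of non-converters.
- The covariate does not vary, so a Cox hazard ratio cannot be estimated.

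**3. Some participants below 24 (q > 0).** True positives cannot exceed all positives, so sensitivity ≤ (q × 400)/(incidence × 400) = q/incidence. This ceiling is reached only if every positive converts.

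| q (assumed) | Positives of 400 | Ceiling, incidence 40% | Ceiling, incidence 27% |
|---|---|---|---|
| 1% | 4 | 2.5% | 3.7% |
| 2% | 8 | 5% | 7.4% |
| 5% | 20 | 12.5% | 18.5% |
| 10% | 40 | 25% | 37.0% |

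To reach even 52%, the low end of the article's literature range, q must be at least 0.52 × 0.40 = 20.8%, or 0.52 × 0.27 = 14.0% at the lower incidence.

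**4. Information for a hazard ratio.** With 160 events, an illustrative hazard ratio of 2 and a two-sided 5% test, the Schoenfeld approximation gives power = Φ(ln 2 × √[160 × q(1 − q)] − 1.96): 99% at q = 50%, 75% at q = 10%, 48% at q = 5%, 23% at q = 2%, 14% at q = 1%.

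**5. The selection rule.** A near-constant variable adds almost nothing to discrimination. Its loss against continuous MMSE is therefore about equal to what continuous MMSE adds. That loss is small only if continuous MMSE also adds little. No numerical limit is set for a small loss, and non-linearity gives a second route to a categorical form.

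**The case against.** The best reply is that the plan already provides for this. It plans the continuous form, and after Table 3 it says that the listed cut-offs do not suit this population and adds cut-offs derived by ROC in the cohort. MMSE thus has three planned forms, and only one fails. That stands.

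A reader might infer that MMSE will be wrongly reported as non-predictive and drop out of the final model. The article does not support this. If continuous MMSE predicts well, the comparison will show a large loss for the below-24 form and the rule will not choose it. If the form is constant, it cannot be fitted at all. If continuous MMSE also adds little, a report of weak prediction is broadly right. The section also ends with a check that no significant biomarker was left out. What remains is a residual risk, from the undefined size of a small loss and from the non-linearity route.

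A reader might also infer that anyone coded abnormal would reflect only disagreement between two correction tables. That goes too far. The article names correction sources for the analysis but none for entry. Education versus sex may be a wording slip, and scores below 24 could also come from protocol deviations or from a gap between the screening and baseline scores.

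Finally, an empty category would be noticed at the first tabulation, and no other biomarker is affected. This limits the severity but does not make the rule workable as written.

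**Conclusion.** The point holds for the Table 3 categorical form of MMSE. The category is empty if entry and analysis use the same score, and otherwise can be expected to be nearly empty. If empty, sensitivity is 0%, specificity 100%, and the positive predictive value, positive likelihood ratio and hazard ratio are unavailable. If not, sensitivity is capped at q/0.40 at 40% incidence: 5%, 12.5% and 25% at q of 2%, 5% and 10%. The emptiness under a common score is a matter of logic; the q values are assumptions, because the article gives no count.

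The literature comparison is therefore uninformative for this form, and the Table 3 preference should not apply to it. The continuous form and a cohort-derived cut-off stay usable, on a range truncated at 24. Severity is moderate: one rule fails as written, but the biomarker and the primary model do not depend on it.

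**What to change.** - Remove the below-24 category for MMSE from the text of Statistical analysis method and from Table 3.
- In Statistical model and variable selection, exempt MMSE from the preference for Table 3 thresholds.
- Use MMSE in continuous form, or with a cohort-derived cut-off above 24 as the paragraph after Table 3 already allows. If a cut-off is used, derive it afresh within each bootstrap sample; the Internal validation section names only the stepwise selection as repeated.
- Report how many participants score below 24 at baseline, and state that entry truncates the MMSE range wherever its accuracy is compared with the literature.
- Reconcile the two descriptions of the correction, or explain why they differ. The article alone does not show which is meant.

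The cost is SAP wording, one count, the loss of one uninformative table row and, if a cut-off is used, one extra step in the bootstrap code. No new data and no change to eligibility are needed.

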For CSF biomarkers, the following fluid levels are considered: threonine-181 (p-tau), total-tau (t-tau), amyloid-beta Aβ1-42, Aβ_1-42/1–40_ ratio, Aβ_1-42_/p-tau ratio. ^18^Fluorodeoxyglucose positron emission tomography (^18^F)FDG-PET is analysed with voxel-based single subject using the optimised procedure based on statistical parametrical mapping (SPM), involving a large database of normal controls for comparison and the new FDG atlas for normalisation [10, 11]. Two techniques are used to compute the right and left hippocampal volumes, normalised to the intracranial volume in volumetric MRI. The first technique is ACM-Adaboost, which is a machine learning algorithm used to classify the voxels belonging to the hippocampal region. The second technique is Freesurfer v6.0, which is a surface-based approach [12]. Seven parameters of Small World (SW) are computed in delta, theta, alpha1, alpha2, beta1, beta2 and gamma frequency bands to evaluate the brain connectivity via graph theory in EEG [13]. As part of the study, each participant is required to undergo all necessary tests for biomarker acquisition. These tests are required to be completed within 60 days from the neuropsychological battery assessment and the acquisition of informed consent at the beginning of the study. Biomarker testing is conducted in a blinded manner, meaning that the data collected at baseline, including predictor variables such as biomarkers and any information related to medical history or clinical examination, are not taken into account during biomarker testing. Moreover, to improve the predictive accuracy of biomarkers, clinical and demographic characteristics will be also considered. A critical review of the relevant literature was conducted to identify factors associated with the development of dementia [14, 15]. The following predictors, selected according to the clinical relevance among all the demographic and clinical variables collected, will be used in the development and validation of the multivariable prediction model: sex, age, level of education (measured in years of education), type of MCI (amnesic, non-amnesic) according to single or multiple domains, Amsterdam IADL (short version) [16], Cumulative Illness Rating Scale (CIRS) including severity and comorbidity index [17], hypertension, family history of dementia, smoking status, status of cohabitation as a proxy of social isolation, psychiatric disease (past and present) and cardiovascular disease. All these data, collected during the clinical assessment visit, could significantly improve the accuracy of the prediction model. All predictors are collected at baseline.

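### EEG is judged only as a transported normal/abnormal label, while MMSE, DFR, CSF and MRI also get a continuous form and cut-offs re-derived for MCI

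*SAP article*

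**What the plan says.** The Predictors section describes continuous EEG measurements: "Seven parameters of Small World (SW) are computed in delta, theta, alpha1, alpha2, beta1, beta2 and gamma frequency bands". The Statistical analysis method section then turns them into one label: "the classification of results into normal or abnormal based on the SW values will be performed by the expert centre". The tool is a fine Gaussian support vector machine, and "This ML classification model has been trained on external data including both healthy individuals and individuals with AD". It is applied to the study cohort as it stands. The EEG row of Table 3 gives physiological versus pathological and nothing else.

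Four marker groups are treated differently: "The evaluation of biomarkers for MMSE, DFR, CSF parameters and MRI measures will be conducted considering the continuous form and the categorical form". The paragraph after Table 3 gives the reason for looking beyond the published thresholds: "these cut-offs were determined to discriminate between normal cognition and AD, but the population under study is at higher risk". Its remedy is limited in scope: "for continuous biomarkers the receiver operating characteristic (ROC) curves will be used to identify new optimal cut-offs for the specific population under study".

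Under Statistical model and variable selection, the article notes that "any categorisation implies a loss of information" and lets performance decide, biomarker by biomarker, between the continuous and the categorical form. The Table 3 threshold is preferred where the loss is small. All biomarkers then enter one stepwise selection. Under Predictive performance, the added value of each is measured by the difference in c-statistics, the category-free NRI and a likelihood ratio test.

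**The concern.** The plan states two premises and applies them unevenly. The first is that a boundary set between normal cognition and AD does not fit people with MCI. The second is that dichotomising costs information. Both apply to the EEG label, which is a dichotomy from a classifier whose training data included healthy and AD individuals. EEG nevertheless gets neither a continuous form nor a boundary adapted to the cohort, and the form-choice rule has nothing to choose between.

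The primary aim is to find which biomarker or set of biomarkers predicts conversion. If EEG ranks low or is removed by stepwise, the planned analyses cannot separate three explanations: EEG connectivity carries little information on conversion, the transported boundary sits in the wrong place for MCI, or the dichotomy has discarded the useful part.

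**Working it through.** **Text against text.** The forms in which each marker is evaluated, from the Statistical analysis method section and Table 3:

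| Marker | Continuous form | Categorical form | Cut-off re-derived in the cohort |
|---|---|---|---|
| MMSE, DFR, CSF, MRI | yes | yes | yes, by ROC |
| EEG | no | yes, external classifier | no |
| FDG-PET | no | yes, read at the expert centre | no |
| APOE | no | yes, none/one/both alleles | not applicable |

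EEG is therefore at a disadvantage to four marker groups and not to FDG-PET or APOE. APOE is discrete by nature, and no single score is described for FDG-PET. EEG is the marker for which the article describes both continuous underlying values and a classifier trained on data including healthy and AD individuals.

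**Illustration of what a label can cost.** The article gives no AUC for EEG and no operating point of the classifier in MCI, so both are assumed. Assume equal-variance normal scores in converters and non-converters:

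- Separation: d = √2 · Φ⁻¹(AUC).
- For a cut at c: specificity = Φ(c) and sensitivity = 1 − Φ(c − d).
- The AUC of the resulting binary marker is (sensitivity + specificity)/2. It is largest at c = d/2, where it equals Φ(d/2).

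For AUC 0.75, d = 1.414 × 0.6745 = 0.954. At the best cut, Φ(0.477) = 0.683. With the cut 1 SD higher, c = 1.477, sensitivity is 0.300, specificity is 0.930, and the AUC is (0.300 + 0.930)/2 = 0.615.

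| Continuous AUC (assumed) | d | Best cut | Cut off by 0.5 SD | Cut off by 1 SD |
|---|---|---|---|---|
| 0.65 | 0.545 | 0.607 | 0.595 | 0.566 |
| 0.70 | 0.742 | 0.645 | 0.628 | 0.590 |
| 0.75 | 0.954 | 0.683 | 0.663 | 0.615 |
| 0.80 | 1.190 | 0.724 | 0.701 | 0.644 |

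Over this range the loss is 0.04 to 0.08 at the best cut (0.650 − 0.607 to 0.800 − 0.724). It is 0.06 to 0.10 at a 0.5 SD shift (0.650 − 0.595 to 0.800 − 0.701), and 0.08 to 0.16 at a 1 SD shift (0.650 − 0.566 to 0.800 − 0.644). These are stand-alone AUCs, not the increments over clinical variables by which the plan ranks markers.

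**Optimism of re-derived cut-offs.** 1,000 samples of 400 were simulated, with events at 16%, 27% and 40% and the cut chosen as closest to the upper-left corner. For a marker with true AUC 0.70, the apparent (sensitivity + specificity)/2 was 0.659 to 0.664 against a true 0.643. For a useless marker it was 0.518 to 0.525 against 0.500. Re-cutting thus flatters a marker by about 0.02, and a fixed external label gets no such lift. The Internal validation section names only the stepwise procedure as repeated in each bootstrap sample, not the cut-off derivation or the choice of form.

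**The case against.** The strongest reply is that a locked external label is a legitimate, prespecified test of that classifier and avoids in-sample tuning. This stands as a reason to keep the label. It does not make the comparison even when four competing groups may be re-cut on study data.

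Second, the form-choice rule prefers the Table 3 threshold where the loss is small, and categorises where non-linearity is found. Several of the four groups may therefore reach the final stepwise as binary markers on published thresholds, much like EEG. This narrows the gap but does not close it: that loss is judged against a continuous form, and EEG has none.

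Third, the raw decision value of a Gaussian-kernel classifier is not a calibrated severity scale and need not be linear or monotone in conversion risk. This stands, and it limits both the remedy and the illustration, which assumes monotonicity.

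Fourth, the Discussion concedes that categorisation was partly chosen for clinical use. That is a general statement, and it does not explain why the remedy reaches some markers and not EEG.

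A reader might also infer more than the document supports:

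- *EEG is disadvantaged against every competitor.* It is not, because FDG-PET and APOE are categorical only as well.
- *The expert centre already computes and can export a decision score.* The article says only that the Small World parameters are computed and that a normal/abnormal result is issued.
- *The classifier saw only healthy and AD individuals.* The wording is that the training data included both; the full training set is not described.
- *EEG will be wrongly dropped, with a loss of the size tabulated above.* Nothing in the document fixes either the direction of EEG's true value or the amount.

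**Conclusion.** The concern holds as an inconsistency of treatment. The plan's own case against normal-versus-AD thresholds and against categorising is not carried through to EEG, which is handled less favourably than MMSE, DFR, CSF and MRI. A poor EEG result would therefore be ambiguous between the marker and this classifier's label.

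The size for EEG cannot be computed from the document. The illustrated AUC losses of 0.04 to 0.16 rest entirely on the binormal model, on assumed continuous AUCs of 0.65 to 0.80, and on cuts up to 1 SD from the best one. They show what a label can cost and do not estimate what it costs here. The change is worth making because it is cheap and removes an ambiguity in the primary question. The document does not show that the planned conclusion on EEG would be wrong.

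**What to change.** In the Statistical analysis method and the Statistical model and variable selection sections:

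1. Add EEG to the markers evaluated in both continuous and categorical form. Use one number per participant: the decision score of the locked external classifier, if the expert centre can export it, with no retraining on study outcomes.
2. Check the functional form of the score, then apply the same ROC cut-off derivation and form-choice rule as for MMSE, DFR, CSF and MRI.
3. In the Internal validation section, repeat any re-derived cut-off and the choice of form inside each bootstrap sample, together with the stepwise selection.
4. Keep the locked binary label for comparison with the literature.
5. If no score can be exported, state that a low EEG rank applies to this classifier's label and not to EEG connectivity as such.

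The cost is SAP wording and, if the score is available, one exported variable. No new test is needed. Only one form enters the final model, so EEG still takes one parameter if the score is used linearly. The downsides are that one more form of one biomarker passes through the form-choice step, and that the score may prove non-linear or non-monotone in conversion risk. In that case the plan's own rule would lead back to a categorical form.
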